### Secondary objectives

To compare the efficacy of ACT in reducing psychological inflexibility with the waitlist control group across three-time points (T0 = baseline assessment, T1 = 4 weeks, immediately after completion of the intervention, T2 = 6 months after commencement of the intervention, and T3 = 12 months after commencement of the intervention).To compare the efficacy of ACT in reducing depression and anxiety compared with the waitlist control group across three-time points (T0 = baseline assessment, T1 = 4 weeks immediately after completion of the intervention, T2 = 6 months after commencement of the intervention, and T3 = 12 months after commencement of the intervention).To compare the efficacy of ACT in enhancing QoL compared with the waitlist control group across three-time points (T0 = baseline assessment, T1 = 4 weeks, immediately after completion of the intervention, T2 = 6 months after commencement of the intervention, and T3 = 12 months after commencement of the intervention).To compare the efficacy of ACT in enhancing social support compared with the waitlist control group across three-time points (T0 = baseline assessment, T1 = 4 weeks, immediately after completion of the intervention, T2 = 6 months after commencement of the intervention, and T3 = 12 months after commencement of the intervention).To evaluate the mediating role of psychological inflexibility and disease acceptance in the relationship between ACT and QoL in breast cancer patients following ACT intervention.To assess the moderating role of social support in the relationship between ACT and Psychological inflexibility in breast cancer patients.

## Methods

### Ethic

Ethical approval for this study was obtained from the Jawatankuasa Etika Penyelidikan Manusia, Universiti Sains Malaysia (JEPeM-USM), with approval granted on 19th December 2022 (JEPeM Code: USM/JEPeM/22080569). The approval was subsequently extended from 19th December 2023 to 18th December 2024. All procedures performed in studies involving human participants were in accordance with the ethical standards of the institutional and/or national research committee and with the 1964 Helsinki Declaration and its later amendments or comparable ethical standards.

Regarding the consent process for our study, we will obtain written consent from all participants. Participants will receive a Subject Information and Consent Form detailing the study’s purpose, procedures, risks, benefits, and their rights as participants. Additionally, participants were given a Participant’s Material Publication Consent Form to provide explicit consent for the publication of anonymized data or materials derived from their participation in the study. They will be given sufficient time to review the document and ask any questions before providing their signature indicating their voluntary participation. As our study did not involve minors, we did not need to obtain consent from parents or guardians.

### Trial registration

This study is registered in ClinicalTrials.gov under the registration number NCT05327153.

### Study design

This study will employ a double-blind, parallel-group randomized controlled trial to evaluate ACT’s effectiveness in promoting disease acceptance among breast cancer patients. This research protocol was developed in accordance with the SPIRIT (Standard Protocol Items: Recommendations for Interventional Trials) guidelines.

### Randomization and allocation concealment

Permuted block randomization with an allocation ratio of 1:1 is carried out. Participants will be randomly assigned based on odd (Group A) and even (Group B) rows using a computer-generated randomisation sequence. The randomization sequence, informing participant assignment to either intervention (Group A) or waitlist control (Group B) condition, is provided in opaque envelopes by one investigator not involved in participant recruitment or assessment. Blinded to the study assignment, participants will be allotted to either group in a 1:1 ratio. Participants will be randomly assigned to two groups: the intervention group receiving ACT intervention or the control group receiving standard treatment with non-therapeutic intervention.

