### Participants

Patients receiving treatment in oncology clinics at Universiti Sains Malaysia and Hospital Seberang Jaya will be recruited for the study. The criteria for study participation include: (1) diagnosed with breast cancer, (2) aged 18 years or older, (3) currently receiving treatment, (4) able to understand and communicate in the study language, and (5) willing to participate in the intervention and follow-up assessments. Patients are deemed ineligible for the study if they: (1) have severe cognitive impairment or significant psychiatric comorbidities (e.g., psychosis, substance abuse) that could hinder their participation in the study, (2) are diagnosed with malignant tumors, and (3) currently receiving any other form of psychological therapy intervention.

Sample size calculations will be based on power analysis using established effect sizes from previous studies on ACT interventions and disease acceptance among similar populations. We conducted an a priori power analysis using GPower 3.1.9.7 to calculate the estimated sample size needed for mixed ANOVA with control of three covariates: the type I error was 0.05, with a power of 0.95, three covariates, with two intervention groups and an effect size of 0.46 by referring to an RCT on the efficacy of ACT on illness cognition among breast cancer patients [28], Hence, the estimated sample size needed is 80 (with the inclusion of a 20% dropout rate). Hence, 40 subjects are required per group.

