## Outcomes

Participants will be asked to complete self-report questionnaires in person or through secure online platforms. The questionnaires will cover various aspects, including demographic information such as age, race, educational background, marital status, and employment position. Disease-related information, such as the disease stage, current treatment, and other relevant factors, will also be gathered. Then, we need assessments of the primary and secondary outcomes. We use the electronic data capture system (EDC) to capture and store the data.

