### Mixed ANOVA analysis

The comparison of mean differences before and post-intervention will be examined to see whether any changes in illness cognition, anxiety, depression, psychological inflexibility, QoL, and social support among breast cancer patients in response to ACT intervention. Then, while controlling for confounders, mixed ANCOVA will be used to look at any significant changes in the measured variables between the waiting and intervention groups, with the group as the between-group factor and time as the within-group factor. A few confounding factors that may affect disease acceptance in cancer will be taken into account and controlled by using mixed ANCOVA, such as the level of pain and fatigue and monthly income [42, 43]. Age is also included as a covariance.

The effect sizes will be determined to evaluate how much patients’ perceptions of the measured variables changed with and without an ACT intervention. The formula of Cohen’s d (Rosnow Rosenthal, 1996) [44] is used to calculate the effect size. According to Cohen (1988), the effect size will be considered small if (d = 0.2), medium (d = 0.5), and large (d = 0.8).

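### Two hospitals and a clinically mixed population, but no stratification factor in the allocation and neither hospital nor stage among the named covariates: a cheap gain in balance and precision is left unused

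*Protocol article*

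**What the plan says.** Under Randomization and allocation concealment, the article states: "Permuted block randomization with an allocation ratio of 1:1 is carried out". It continues: "Participants will be randomly assigned based on odd (Group A) and even (Group B) rows using a computer-generated randomisation sequence". One investigator supplies the sequence in opaque envelopes. The section describes one sequence. It names no stratification factor and does not say how the envelopes are held or shared between hospitals.

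Under Participants there are two recruiting sites: "Patients receiving treatment in oncology clinics at Universiti Sains Malaysia and Hospital Seberang Jaya will be recruited for the study". The disease-related inclusion criteria are broad: "1) diagnosed with breast cancer, (2) aged 18 years or older, (3) currently receiving treatment". No limit is set on stage, type of treatment or time since diagnosis. (One exclusion, "2) are diagnosed with malignant tumors", conflicts with the first inclusion criterion if read literally, and the two must be reconciled. This point follows the inclusion list.)

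Under Outcomes, stage and treatment are to be recorded: "Disease-related information, such as the disease stage, current treatment, and other relevant factors, will also be gathered". Under Mixed ANOVA analysis, the confounders to be controlled are introduced as "such as the level of pain and fatigue and monthly income [42, 43]. Age is also included as a covariance". Under Descriptive analysis, stage at diagnosis, chemotherapy regimen and time since diagnosis are to be tabulated. The groups are to be compared at baseline, but nothing is said about what that comparison would change in the model.

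**The concern.** The Introduction lists body-image change after surgery and the side effects of chemotherapy and radiation among the reasons why patients find it hard to accept their disease, and acceptance is the primary outcome. The Limitations section acknowledges that the participants are heterogeneous. Sessions are delivered while patients attend hospital for treatment, so the setting may differ by hospital. Hospital and stage are therefore plausible prognostic factors. Both can be known before randomisation, and the text as written uses neither in the allocation or in the model.

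In a trial of about 40 per arm, a visible imbalance in such a factor is not rare. What is at stake is precision, and how far readers will trust a single small trial whose arms differ visibly by hospital or stage.

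**Working it through.** **1. The plan's own sample size.** Inputs from Participants: two-group ANCOVA, alpha 0.05, power 0.95, three covariates, effect size 0.46, 20% dropout. The metric of 0.46 is not stated; it is taken here as Cohen's f, which reproduces the result. For a noncentral F test with lambda = f² × N, df1 = 1 and df2 = N − 2 − covariates:
- N = 63: power 0.948.
- N = 64: lambda = 0.46² × 64 = 13.54, df2 = 59, power 0.951.
- 64 / (1 − 0.20) = 80, or 40 per arm, as stated.

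**2. Chance of imbalance with one list used in order of arrival.** The documents do not give the hospital shares or the stage distribution, so these are assumptions.

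Exact hypergeometric with 80 patients, 40 per arm and K patients having the factor:

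| Factor (assumed) | Split or worse | Probability |
|---|---|---|
| Hospital, K = 40 | 24:16 | 0.117 |
| Advanced stage, K = 16 | 11:5 | 0.161 |
| Advanced stage, K = 20 | 13:7 | 0.196 |

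A 24:16 split is 24/40 against 16/40, a difference of 20 percentage points.

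Simulation of 20,000 trials, permuted blocks of 4 (assumed), hospital share 30% or 50% (assumed), hospital totals left to vary:

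| Scheme | Difference ≥ 10 points | Difference ≥ 20 points |
|---|---|---|
| One list for both hospitals | 39% to 43% | 7% to 9% |
| Separate list per hospital | none | none |

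The Abstract gives a target of 90 rather than 80. At 90, the exact probability of a 20-point difference is 0.02 to 0.09 for factor prevalences of 20% to 50%.

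**3. What a 24:16 split would do to the estimate.** Shift in an unadjusted comparison at one time point = hospital difference × 0.20:
- 0.3 SD × 0.20 = 0.06 SD
- 0.5 SD × 0.20 = 0.10 SD
- 0.8 SD × 0.20 = 0.16 SD

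The standard error of a difference with 40 per arm is √(2/40) = 0.22 SD.

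The plan, however, is a mixed model with time as the within-patient factor. For the 0.5 SD case, with the hospital difference equal at both times and a residual pre-post correlation of 0.6 (assumed), simulation gives:

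| Contrast | Shift |
|---|---|
| Follow-up score only | 0.10 SD |
| Change (group by time) | about 0.00 SD |
| Follow-up with baseline as covariate | 0.04 SD |

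**4. Cost in power of adding the covariates, at 64 evaluable.** With the four named covariates, power is 0.9514. Adding hospital (1 df) and a two-level stage (1 df) makes six, power 0.9512. Adding hospital and a four-level stage (3 df) makes eight, power 0.9509. The evaluable number stays at 64 and the total at 80. If the added covariates explain 5% to 20% of the residual variance (assumed), power at 64 rises to between 0.960 and 0.981.

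**The case against.** The case against has several parts.

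*Chance imbalance is not bias.* This stands. Randomisation keeps the comparison unbiased, and the type I error already allows for such imbalance. A reader might infer that a hospital or stage imbalance could not be separated from the ACT effect. The planned model does not support that: a stable difference is present at baseline and at follow-up and largely cancels in the group-by-time contrast. The shift of 0.06 to 0.16 SD belongs to a comparison at a single time point, and even there it is smaller than one standard error.

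*The envelope mechanism is not stated.* This also stands. A reader might infer that one series shared by two hospitals must break the blocks within each hospital. If the series were divided in runs of whole blocks, every block would balance within its hospital. The imbalance figures apply only if one series is used across both in order of arrival, which the article neither says nor rules out.

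*This is silence in a condensed article.* Partly. The absence of stratification is inferred from a single described sequence with no factor named. The covariate list is introduced as examples, the article refers to an analysis plan that is not shown, and pain and fatigue may partly stand in for stage. But the article does describe the allocation and does name covariates, and an analysis plan written later cannot change the list structure. If hospital-specific lists already exist, one sentence settles the matter.

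*Unstratified permuted blocks are an accepted design at this size.* True, which makes this an improvement rather than the correction of an error.

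**Conclusion.** The point holds as a specific, nearly free improvement. As described, the trial takes patients of any stage and treatment type from two hospitals with one permuted-block sequence, and it names neither hospital nor stage as a covariate. If one series is used in order of arrival, a 20-point hospital imbalance has probability of about 12% with equal hospital totals, or 7% to 9% with totals left to vary. Both figures rest on assumed hospital shares, and the second also on an assumed block size of 4.

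The consequence is some lost precision and credibility. It matters mainly if hospital or stage influences change over time, or if arms are compared at one follow-up. The documents give no figure for a hospital or stage effect, so the size of the loss cannot be fixed from them. They do not support a claim of confounding, of an invalid test or of an underpowered trial.

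**What to change.** - **Allocation:** generate a separate permuted-block 1:1 list, with its own envelope series, for each hospital. If this is already the arrangement, say so in the section on randomisation.
- **Analysis:** pre-specify hospital and baseline disease stage as covariates in the primary mixed ANCOVA, alongside those already named, and state how stage will be grouped.
- **If enrolment has begun:** leave the allocation as it is and make the covariate change alone.

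The cost is a second list and envelope set, a sentence or two of text and a few degrees of freedom. Stage is already collected and hospital is known for every patient. No extra patients are needed.

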### Blinding

Participants will be unaware of the study’s randomization into the designated groups, which will be carried out by a research assistant who is not otherwise involved. As a result, participants will not be informed of the group to which they are allocated.

Additionally, to minimize bias, the ACT intervention group and the control group will receive a 4-session program (with one hour per session, one session per week for 4 weeks). Participants in the control group will also receive equal attention (attentive listening) and time from the professional figure administering the program with non-therapeutic intervention(the participants in the control group are given equal duration of the session, number of sessions, duration of intervention and attended by the same therapists who conducted the ACT group. The participants will also be attended to with active listening by the therapists in the control group).

To maintain blinding throughout the study, the researchers will be blinded to participants’ randomized assignments into the groups. This process will be carried out by a research assistant who is not involved in the study. Additionally, data collection for this study will be conducted by the same research assistant, ensuring impartiality. The research assistant will remain unknown to the study’s hypotheses. Furthermore, data analysis for the study will be performed by statisticians who are not involved. The statistician will utilize a statistical analysis plan to conduct data analysis before the final unblinding of the data lock.

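### The research assistant who carries out the randomization also collects the outcome data, so the double-blind label is unsupported; an odd/even rule that conflicts with permuted blocks leaves concealment in doubt.

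*Protocol article*

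**What the plan says.** Four parts of the protocol article bear on this point.

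- **Study design** gives the label without qualification: "This study will employ a double-blind, parallel-group randomized controlled trial".
- **Randomization and allocation concealment** names the method, "Permuted block randomization with an allocation ratio of 1:1 is carried out", and then gives the rule: "Participants will be randomly assigned based on odd (Group A) and even (Group B) rows using a computer-generated randomisation sequence". The same section identifies Group A as the intervention and Group B as control. It adds that the sequence "is provided in opaque envelopes by one investigator not involved in participant recruitment or assessment".
- **Blinding** gives the randomization to an assistant, "which will be carried out by a research assistant who is not otherwise involved", and repeats the point: "This process will be carried out by a research assistant who is not involved in the study". It then says that "data collection for this study will be conducted by the same research assistant, ensuring impartiality". The only masking stated for this person is "The research assistant will remain unknown to the study’s hypotheses", which I read as meaning that the assistant does not know the hypotheses. The section also says that researchers are blinded to assignment, that participants are not told their group, that uninvolved statisticians analyse before unblinding, and that the same therapists run both arms.
- **Outcomes** says that participants complete self-report questionnaires, either in person or online.

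**The concern.** There are two separate matters, and they should be kept apart.

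The first is blinding after assignment. The primary outcome is a questionnaire. If the person who hands it over, explains it or chases missing items knows who received ACT, that knowledge can affect responses and completeness differently by arm. The article presents the arrangement as a safeguard, so a reader of the results would credit the trial with a protection that its own role assignments do not provide.

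The second is concealment before assignment. If a recruiter can foresee the next allocation, enrolment can be selective and the arms may differ from the start. Whether that is possible here depends on what the odd/even rule means, and the text does not settle this.

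**Working it through.** The plan states no figure on this point. The first two steps compare the text with itself, and the third gives the arithmetic for predictability.

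**1. The assistant's roles (Blinding section)**

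| Statement | Consequence |
|---|---|
| Carries out the randomization | Ordinarily knows each allocation |
| Has no other involvement, and is outside the study | Cannot also be the data collector |
| Collects the data | Contradicts the row above |
| Does not know the hypotheses | Is not thereby masked to allocation |

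No statement masks this person to allocation. Using the letters A and B would not help, because the article says which letter is which arm. No other data collector is named, so as written all outcome data pass through someone who knows the allocation.

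**2. Who is blind, party by party**

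- Participants: not told their group. They do experience the sessions, and under Procedure they receive a full explanation of the aims before consenting.
- Therapists: the same ones deliver both arms, so they know the arm.
- Data collector: knows the allocation as written.
- Researchers: stated to be blinded. The investigator who supplies the sequence in envelopes is likely to have seen it, so this statement already needs an exception.
- Analysing statisticians: stated to work before unblinding.

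**3. The allocation rule**

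In a permuted-block list, the order of A and B within each block is random. A rule that odd rows are A and even rows are B fixes the order once the rows are fixed. Two readings are open.

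- *Rows follow enrolment order.* The list is A, B, A, B. With the published key every assignment is known: 100%. If the starting letter were unknown, the first guess has probability 0.5 and all later ones are certain. With the 80 participants of the sample-size paragraph this is (79 + 0.5)/80 = 99.4%.
- *Odd/even only labels rows that the computer then puts in random order.* The printed key reveals nothing while the list is hidden, and predictability is that of permuted blocks.

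For the second reading, suppose someone knows the block size and all earlier assignments and always guesses the arm with more places left. With block size b = 2m, the expected number of correct guesses per block is m − 1/2 + 2^(2m−1)/C(2m, m). The expected share of assignments that are certain is 1/(m + 1). The article gives no block size, so the sizes are assumed.

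| b | Correct per block | Best-guess rate | Certain share |
|---|---|---|---|
| 2 | 1 − 0.5 + 2/2 = 1.50 | 75% | 50% |
| 4 | 2 − 0.5 + 8/6 = 2.83 | 71% | 33% |
| 6 | 3 − 0.5 + 32/20 = 4.10 | 68% | 25% |
| 8 | 4 − 0.5 + 128/70 = 5.33 | 67% | 20% |
| 10 | 5 − 0.5 + 512/252 = 6.53 | 65% | 17% |

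Enumerating every possible block of each size gives the same rates. The fair contrast is therefore 100% against 65% to 75%. A coin-toss rate of 50% is not the right comparator for a permuted-block design.

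**The case against.** The strongest defence concerns concealment. A reader might infer that allocation is simple alternation and that concealment therefore fails. The text does not say so. It names permuted blocks, ties the rows to a computer-generated sequence and describes opaque envelopes supplied by someone outside recruitment and assessment. Consecutive recruitment, stated under Procedure, makes enrolment order a natural reading, but not the only one. This objection stands: concealment is in doubt and no more.

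A reader might also infer that the assistant's double role breaks concealment. It does not. The article does not say that the assistant recruits, so this is a blinding defect that arises after assignment. Nor is there a necessary conflict between an investigator who supplies envelopes and an assistant who carries out the assignment, because preparing and implementing are compatible tasks.

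On blinding, several stated protections are real. The control arm is matched for sessions, time and therapists. The assistant does not know the hypotheses, analysis precedes unblinding, and online completion reduces contact with the collector. The article never claims that therapists are blind, and a double-blind label does not by itself assert it. The stronger objection to the label is the data collector. These protections limit the risk but do not remove it where forms are completed in person, and they do not resolve the contradiction about the assistant. Self-report response bias is listed under Limitations and future research, but participant expectancy is not.

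Block size and similar detail may properly sit in the full protocol, so their absence is not counted here.

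**Conclusion.** The blinding part is wrong as written. One person is given both the randomization and the data collection, is twice described as having no such involvement, and is masked only to the hypotheses. Blinded data collection, and with it the unqualified double-blind label, is not supported. This rests on one ordinary assumption: whoever carries out an assignment knows it. The extent is all outcome data, since no other collector is named. The documents give no basis for putting a size on any resulting bias, and the share of questionnaires completed in person is not stated.

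The allocation part is an inconsistency that must be reconciled. Odd/even rows and permuted blocks are different schemes. If rows follow enrolment order, predictability is 100% and envelopes cannot hide the pattern. If they do not, it is at most 65% to 75% for assumed block sizes of 10 to 2, and that only for someone who knows the block size and the earlier assignments.

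**What to change.** 1. Delete the odd/even rule. Assign from the computer-generated permuted-block list, prepared by someone who does not recruit, assess or analyse. The analysing statistician should not prepare it, because that would undo the blinded analysis.
2. Have the investigator who already supplies the envelopes, and who is outside recruitment and assessment, carry out the allocation. Exempt that one person from the statement that researchers are blinded.
3. Confine the research assistant to data collection, masked to allocation as well as to the hypotheses, and correct the two descriptions of that person as uninvolved.
4. Replace the double-blind label with a statement of who is blinded (data collector and analysing statistician, with participants not told their group) and who is not (therapists and the allocating investigator).
5. Name participant expectancy as a limitation.

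The cost is a swap of existing roles and a less favourable design label. Randomly varying block sizes or stratification by hospital would be reasonable options, but this point does not require them.
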